### 10.3.5. significance level

Unless otherwise noted, the significance level is 5% one-sided, and the confidence coefficient for the confidence interval is correspondingly 90% two-sided.

### 10.3.6 Handling of Missing Data, etc.

Missing values are not compensated for, and unless otherwise noted as the analysis method, the analysis is performed without using the completion method.

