#### **5.5. post-treatment**

After discontinuation of protocol treatment or completion of protocol treatment, post-treatment is not restricted.

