#### **5.6. discontinuation of protocol treatment**

The investigator or subinvestigator will discontinue the study drug if the investigator or subinvestigator determines that continuation of protocol treatment is not feasible for any of the following reasons. The date, reason, and progress of discontinuation will be documented in the medical record and the case report form (CRF), and necessary tests will be performed at the time of discontinuation or dropout to evaluate efficacy and safety.

If the drug is discontinued due to the occurrence of an adverse event, the patient should be followed up as much as possible until the current status is restored.

(1) When a research subject or a surrogate withdraws from participation in clinical research or withdraws his/her consent.

(2) When it is found that eligibility is not satisfied after registration

(iii) When the underlying disease is completely cured and there is no longer a need for continued administration

(iv) When it is determined that continued administration of the test drug is not desirable due to worsening of the underlying disease

(5) When it is difficult to continue the clinical research due to exacerbation of complications

(6) When it is difficult to continue the clinical research due to adverse events

(vii) In case of significant non-adherence (when it is determined that less than 70% of the total scheduled doses will be taken or more than 120% of the total scheduled doses will be taken)

(viii) If the research subject does not come to the hospital due to relocation, etc.

(ix) When the entire clinical research is discontinued

(10) When the principal investigator determines that it is appropriate to discontinue the clinical research for other reasons

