### **9. endpoint definition**

#### **9.1. main endpoints**

Primary Endpoint: Tumor response assessed by MRI-based volumetric analysis at 6 months, defined as at least a 20% reduction in volume. For diffuse lesions, reduction in the primary lesion size will be assessed.

Rationale: Based on past case series, a measurable degree of shrinkage is expected at 6 months of drug administration.

Prior to lesion evaluation, a definitive diagnosis is made by the imaging evaluation committee to determine efficacy.

Methods of measuring lesions

1. MRI is performed.

Required imaging methods:

T1WI; T1-weighted image, T2WI; T2-weighted image, T2FS; T2 fat suppressed image, 3D-T2FS; 3D-T2 fat suppressed image. In all cases, axial sectioning is mandatory.

Gd-T1FS; post-contrast T1 fat suppression images are not required and may be taken only when necessary for differential diagnosis.

T2 fat-suppressed images should be taken in gapless mode. The basic slice thickness is 3-5 mm, but if the lesion is large, 6-8 mm is acceptable.

Definitive evaluation is based on volume comparison, using 3D-T2FS, or if 3D-T2FS is not available, T2FS with gapless imaging.

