## **10. statistical considerations**

### **10.1 Basis for Setting Target Number of Cases**

In our retrospective case series study, the response rate (20% volume reduction at 6 months) to treatment with Eppikajutsuto in LM patients was 83% (in submission). Conservatively taking into account the overestimation tendency of the retrospective study design of prior reports, we expect a response rate of at least 50% with this treatment in the study's patient population. In the same study, none of the patients had a response to no treatment, and both patients had an increasing trend. Considering the exploratory nature of this study, the first prospective clinical trial, the number of patients will be designed based on accuracy. The lower limit of the two-sided 90% confidence interval (corresponding to a one-sided significance level of 5%) is 29.1% (the upper limit is 70.8%) if 9 patients respond (response rate of 50%) in the 18 patients in the analysis.

Considering that the main purpose of this exploratory study is to collect information that can be used for the next phase of the study, we believe that 18 cases is an appropriate number of cases. Since the number of patients seen annually at each site is approximately 5 cases each, it is possible to enroll the target number of cases in 3 years.

Based on the above considerations, the target number of cases was set at 20 to ensure accuracy in case a few cases were excluded from the analysis.

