## **10.3 Analysis Items and Methods**

### **10.3.1. primary endpoint primary analysis method**

For the primary endpoint of the study, the response rate will be based on whether or not patients achieve a reduction in lymphatic malformation volume by volumetry of at least 20% from the pre-treatment level at 6 months of treatment with the drug. An exact method based on a binomial distribution will be used for interval estimation. The significance level for the main analysis is 5% one-sided, and the corresponding two-sided 90% confidence interval is calculated.

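### The no-imputation rule, read naturally, lets treated patients without an evaluable 6-month MRI leave the primary response rate, which can inflate the rate and its lower 90% limit

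*Protocol*

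**What the plan says.** Section 9.1 defines the primary endpoint: "Tumor response assessed by MRI-based volumetric analysis at 6 months, defined as at least a 20% reduction in volume". Section 10.3.1 turns it into a proportion: "the response rate will be based on whether or not patients achieve a reduction in lymphatic malformation volume by volumetry of at least 20" (per cent, from the pre-treatment level). On the interval it says: "An exact method based on a binomial distribution will be used for interval estimation", and "The significance level for the main analysis is 5% one-sided, and the corresponding two-sided 90% confidence interval is calculated".

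Section 10.2 places the primary analysis in the FAS. It removes four kinds of patient: a confirmed ineligible diagnosis, violation of an important exclusion criterion, no protocol treatment at all, and no data at all since enrolment. Lacking a 6-month MRI is not among them.

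Section 10.3.6 sets the missing-data rule: "Missing values are not compensated for, and unless otherwise noted as the analysis method, the analysis is performed without using the completion method".

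Section 5.6 lists reasons for stopping. They include worsening ("iv) When it is determined that continued administration of the test drug is not desirable due to worsening of the underlying disease"), adverse events, taking less than 70% of scheduled doses, and complete cure. It asks for tests of efficacy and safety at the stop, and the schedule in 6.2 appears to include an MRI there. Section 5.5 adds: "After discontinuation of protocol treatment or completion of protocol treatment, post-treatment is not restricted".

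**The concern.** In a single-arm trial the response rate and its lower confidence limit are the whole efficacy result, so the denominator has to be fixed in advance. Two sections pull apart. The FAS definition keeps a treated patient with no 6-month image. The missing-data rule gives that patient no response value, and 10.3.1 makes no exception. Counting the patient as a non-responder would assign a value to a missing outcome, which 10.3.6 rules out on its natural reading.

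Several of the stopping reasons in 5.6 are related to outcome. If patients who stopped for worsening, side effects or poor adherence are the ones without a 6-month image, the patients left in the rate are a favourable selection. The PPS comparison would not reveal this, because 10.2 also requires a completed MRI for the PPS. The protocol also does not say whether an image taken at discontinuation may stand in for the 6-month value.

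**Working it through.** **Inputs.** Binary response at 6 months (9.1, 10.3.1); exact binomial two-sided 90% interval (10.3.1); 20 enrolled and 18 analysed, with 9 responders as the planning case (10.1). The protocol does not give the number of patients without a 6-month MRI. Assumption: 2 or 4 of 20, that is 10% or 20%.

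**Formula.** For x responders of n, the Clopper-Pearson 90% limits are: lower = 5th percentile of Beta(x, n − x + 1); upper = 95th percentile of Beta(x + 1, n − x).

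**The plan's own figure.** x = 9, n = 18: lower = Beta(0.05; 9, 10) = 29.12%, upper = Beta(0.95; 10, 9) = 70.88%. Section 10.1 gives 29.1% and 70.8%. It reproduces; the upper limit was truncated rather than rounded.

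**Illustration.** Take 20 treated FAS patients, of whom 10 truly respond. The full-denominator result is 10/20 = 50.0% (30.2% to 69.8%). Now remove those without a 6-month MRI.

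| Who is missing | Observed-case rate | Exact 90% CI |
|---|---|---|
| 2 non-responders | 10/18 = 55.6% | 34.1% to 75.6% |
| 4 non-responders | 10/16 = 62.5% | 39.1% to 82.2% |
| 2, half of them responders | 9/18 = 50.0% | 29.1% to 70.9% |
| 2 responders | 8/18 = 44.4% | 24.4% to 65.9% |
| 4 responders | 6/16 = 37.5% | 17.8% to 60.9% |

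When all the missing are non-responders, the rate rises by 55.6 − 50.0 = 5.6 or 62.5 − 50.0 = 12.5 percentage points. The lower limit rises by 34.1 − 30.2 = 3.9 or 39.1 − 30.2 = 8.9 points. When the missing respond as often as the rest, the rate does not move. When all the missing are responders, it falls by 50.0 − 44.4 = 5.6 or 50.0 − 37.5 = 12.5 points.

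**What counting as non-response does.** In the first two rows it restores 10/20 = 50.0%. In the last two it gives 8/20 = 40.0% and 6/20 = 30.0%, which is too low. That is why a stop for cure needs its own rule, based on the discontinuation MRI.

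**The case against.** The best reply is that the protocol never says these patients leave the denominator. The FAS keeps them, and 10.3.1 asks whether or not a patient achieves the reduction, which can be read as counting anyone without a demonstrated reduction as a failure. This stands as a possible reading, but 10.3.6 points the other way. The two readings give different primary results, and the choice would be open once the data are known. Nor can the matter simply be left to the SAP, because the protocol states a missing-data rule and an SAP that counted these patients as non-responders would have to depart from it.

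It is also fair that nothing cancels the Day 168 MRI after a stop, that 5.3.5 continues monitoring after a stop for poor adherence, and that the PPS wording expects imaging in some stopped patients. The number of missing images may therefore be small. The study is exploratory and states no null rate or decision threshold, so no formal decision turns on a few points.

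Three stronger readings are tempting, and the documents do not support them:

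- **The planning figure shows that patients without MRI are dropped.** Section 10.1 says that "the target number of cases was set at 20 to ensure accuracy in case a few cases were excluded from the analysis" and gives no reason for the exclusions. The four FAS exclusions in 10.2 account for that allowance equally well. It is no evidence of dropping, and 9/18 is correct for 18 analysed.
- **The rate will be inflated.** That depends on who is missing. Stopping for complete cure is a listed reason and biases the rate downward.
- **Rescue treatment will be counted as response to the study drug.** Section 5.5 leaves this possible, but it needs an early stop, another treatment before Day 168, a later MRI, and use of that MRI for the primary endpoint. The protocol gives no frequency for any of these steps.

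**Conclusion.** The point holds as a badly fixed rule for the primary analysis. Sections 10.3.1 and 10.3.6 together, on their natural reading, remove from the rate treated patients whom 10.2 keeps in the FAS, and the role of the discontinuation MRI is left open. For 2 to 4 of 20 patients missing, all of them non-responders, the rate is overstated by 5.6 to 12.5 points and the lower 90% limit by 3.9 to 8.9 points. With the same numbers missing and all of them responders, the rate is understated by the same 5.6 to 12.5 points. Stops for worsening, adverse events or non-adherence make the upward direction plausible; the documents do not make it certain. The size rests on the assumed number missing and on a true rate of 50%, the response rate that 10.1 expects as a minimum.

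**What to change.** In 10.3.1 and 10.3.6, state that:

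- all FAS patients form the denominator of the primary response rate;
- a patient without an evaluable 6-month MRI counts as a non-responder in the primary analysis;
- the discontinuation MRI is used in named cases only, for example to classify a patient who stopped for cure;
- for the analysis, shrinkage on an MRI taken after sclerotherapy, resection or an mTOR inhibitor is not credited as response (this is a counting rule and does not affect what care is given);
- the observed-case rate is reported as a sensitivity analysis.

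The 9/18 planning figure in 10.1 can stay. The cost is about one paragraph of text, with no new visits or data. The reported response rate may be somewhat lower, and it will be too low if patients without an image had in fact responded; the observed-case analysis will show how much depends on this.

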### **3.2 Exclusion Criteria**

A project shall be ineligible if one or more of the following items are met

- 
1. patients with a history of allergic reactions to Koshuyuan
  2. are receiving or have received mTOR inhibitors
  3. who have undergone sclerotherapy or surgery in the past
  4. who have serious diseases other than lymphatic malformations
  5. patients who participated in other clinical studies (trials) within 3 months prior to the start of treatment with the study drug
  6. patients for whom evaluable MRI cannot be performed
- Other patients deemed inappropriate as research subjects by the principal investigator or subinvestigator
- [Rationale] 1)-2)-3)Influence on efficacy evaluation and consideration for safety,  
2)-3)Influence on efficacy evaluation, 4)-7)Consideration for safety

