## 2. evaluation method

Two evaluators (Imaging Evaluation Committee: Diagnostic Radiologist) who meet the following criteria

(1) be an external evaluator, and (2) be a central diagnosis rather than a facility-by-facility evaluation.

OsiriX, a DICOM viewer, shall be used for measurement.

Before evaluation, the evaluators confirm the extent of the lesion to be evaluated in two or more directions, such as axial and coronal sections, and establish the appropriate measurement area. As a rule, the volume is measured using the axial section image.

For the measurement, two evaluators shall independently measure the volume. The measured values shall be rounded off to two decimal places. The average of the two evaluators' final evaluation values shall be the final evaluation value. The inter-observer correlation coefficient (ICC) is calculated to evaluate the reproducibility of the measurement values among the evaluators.

If the respective values differ by more than 10%, it is desirable to confirm the ranges measured by each other, since the ranges and sites to be evaluated may be very different.

After the measurement, all the area and ROI information measured in each slice should be saved as the original data of the measured values. Specifically, the data should be saved in a movie, JPEG image, or other format that separates the evaluation period for each patient, and submitted to the secretariat together with the data of the definitive evaluation value.

The primary evaluation is a comparison of pre-treatment and 6 months post-treatment.

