## **10.2. population to be analyzed**

The primary analysis of the primary and secondary endpoints will be performed on the Full Analysis Set (FAS). Analysis will also be performed on the Per Protocol Set (PPS) and compared with the FAS to confirm the stability and sensitivity of the analysis results.

The FAS is defined as a population that excludes from all enrolled cases any case that falls into one of the following categories: (1) cases with a confirmed diagnosis of a disease that is not eligible, (2) cases that violate important exclusion criteria, (3) cases that have never received protocol treatment since enrollment, or (4) cases with no data at all since enrollment.

The PPS will be defined as patients who meet the minimum requirements for key variables in the study protocol, for whom protocol treatment was not possible or was discontinued, but who have completed MRI evaluation and have no serious protocol violations regarding eligibility criteria, concomitant prohibited drugs, etc. The Safety Analysis Set (SAS) is defined as all enrolled patients, excluding those who have never received protocol treatment since enrollment.

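### The protocol bars any handling of missing values, so on its plainest reading dosed children without a 6-month MRI leave the denominator of the primary response rate, and upward bias is likely

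*Protocol*

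**What the plan says.** - **Endpoint.** In Protocol 10.3.1, "the response rate will be based on whether or not patients achieve a reduction in lymphatic malformation volume by volumetry of at least 20" percent from the pre-treatment level at 6 months. The evaluation method under 9.1 fixes the time point: "The primary evaluation is a comparison of pre-treatment and 6 months post-treatment". Neither place says how to classify a child who has no evaluable 6-month volume.
- **Population.** Protocol 10.2: "The primary analysis of the primary and secondary endpoints will be performed on the Full Analysis Set (FAS"). The FAS removes only children with a wrong diagnosis, an important exclusion violation, no dose at all, or no data at all. A dosed child with blood results but no 6-month MRI therefore stays in.
- **Missing data.** Protocol 10.3.6: "Missing values are not compensated for, and unless otherwise noted as the analysis method, the analysis is performed without using the completion method". Section 10.3.1 notes nothing to the contrary.
- **Sample size.** Section 10.1 plans on 18 analysed children, and "the target number of cases was set at 20 to ensure accuracy in case a few cases were excluded from the analysis".
- **Stopping.** The reasons in 5.6 include "When it is determined that continued administration of the test drug is not desirable due to worsening of the underlying disease", exacerbated complications, adverse events and marked non-adherence. Complete cure and not attending because of relocation are also listed.
- **Scan at stopping.** Section 5.6 calls for tests at discontinuation or dropout so that efficacy can be evaluated, and the schedule in 6.2 marks an MRI in that column. No section says whether this scan may serve as the 6-month endpoint.
- **Sensitivity check.** Section 10.2 compares the FAS with the PPS, and the PPS definition requires a completed MRI evaluation.

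**The concern.** The protocol does not leave missing data to a later document. It fixes a rule, and that rule suits a single-arm yes/no endpoint badly. If a child without a 6-month volume is neither imputed nor counted as a non-responder, the rate describes only the children who were scanned.

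That group is unlikely to be a random part of those dosed. Worsening, complications, adverse events and non-adherence are all plausibly linked to non-response. There is no control arm in which the same selective loss would show, and the FAS-PPS comparison can omit the same unscanned children from both sets.

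The response rate and its exact 90% interval are the main product of this study and are meant to inform the next phase. With about 20 children, each lost scan moves the rate by a few points. Because the role of the discontinuation MRI is also open, it could be settled after the volumes are known.

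**Working it through.** **Inputs from the protocol.** Target 20 children, 18 in the analysis, expected response at least 50%, exact binomial method, two-sided 90% interval (10.1, 10.3.1). **Assumed, because the protocol gives no figure:** the number of missing 6-month scans, and how the loss splits between responders and non-responders.

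**1. The plan's own figure.** The exact (Clopper-Pearson) limits for x responders among n are the 5% quantile of Beta(x, n−x+1) and the 95% quantile of Beta(x+1, n−x). For 9/18 this gives 29.12% to 70.88%. The protocol states 29.1% to 70.8%, so the figure reproduces; the upper limit is truncated rather than rounded.

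**2. Observed-case rate against all-FAS rate.** Take 20 dosed children, 9 observed responders and m missing scans. The observed-case rate is 9/(20−m). With missing counted as non-response it is 9/20 for every m.

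| m | Observed-case rate | Exact 90% CI | Missing = non-response |
|---|---|---|---|
| 0 | 9/20 = 45.0% | 25.9 to 65.3 | 45.0% (25.9 to 65.3) |
| 1 | 9/19 = 47.4% | 27.4 to 68.0 | same |
| 2 | 9/18 = 50.0% | 29.1 to 70.9 | same |
| 3 | 9/17 = 52.9% | 31.1 to 74.0 | same |
| 4 | 9/16 = 56.3% | 33.3 to 77.3 | same |

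The ratio of the two rates is 1/(1−d) for a missing fraction d: 1.11 at 10% and 1.25 at 20%. Each missing scan adds about 2 to 3 points over this range.

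**3. The opposite bound.** If both of 2 missing children had in fact responded, the full result would be 11/20 = 55.0%, and the observed-case 50.0% would be too low.

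**4. Effect on the interval's error rate.** Let the true rate be p = 0.5, with a fraction a of responders and b of non-responders lost. Each child is then an observed responder with probability p(1−a), an observed non-responder with probability (1−p)(1−b), or missing. The observed-case rate averages p(1−a)/[p(1−a)+(1−p)(1−b)]. The chance that the lower limit lies above the truth comes from summing the exact multinomial probabilities over all outcomes for 20 children; its nominal maximum is 5%.

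| Loss: non-responders / responders | Mean observed-case rate | Lower limit above truth |
|---|---|---|
| 10% / 10% | 0.45/0.90 = 50.0% | 3.4% |
| 15% / 5% | 0.475/0.90 = 52.8% | 5.5% |
| 20% / 0% | 0.50/0.90 = 55.6% | 8.7% |

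All three rows lose 10% overall, which matches the plan's step from 20 to 18. Counting missing as non-response averages 45.0%, 47.5% and 50.0% in the same rows, so it is conservative whenever some missing children had responded.

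**The case against.** The strongest reply is that no section states the denominator. Refusing to fill in values does not literally say that a child leaves the FAS, and 10.3.6 allows exceptions noted with the analysis method. The few exclusions expected in 10.1 could be the FAS exclusions themselves, for example a diagnosis rejected by the imaging committee. This stands in part: removal from the denominator is an inference. It is still the plainest reading, because no section offers another way to score the child.

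A second reply is that stopped children should often have a scan, since 5.6 and 6.2 plan one at discontinuation. That is correct and narrows the problem. It does not close it, because the endpoint is tied to 6 months and nothing lets the stopping-day scan stand in for it.

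Two stronger readings are tempting, and the documents do not support them:

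- A reader might infer that treatment failures certainly leave the denominator and that the rate is therefore inflated. Cure and relocation are also stopping reasons, and equal loss in both groups leaves the average at 50.0%. Inflation is likely, not established.
- A reader might combine the FAS rule on "cases that violate important exclusion criteria" with the criterion "patients for whom evaluable MRI cannot be performed" and infer that a failed follow-up scan removes a child from the FAS. That criterion is an entry criterion, confirmed before registration and verified by the registration center under 4.1. A later failed scan does not violate it.

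**Conclusion.** The concern holds in a limited form. The protocol fixes a no-compensation rule for a binary primary endpoint, in a population that can contain children who cannot be classified, and its only planned robustness check cannot detect the consequence.

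At the plan's own allowance of 2 lost from 20, with 9 responders, the choice of denominator separates 50% (29.1 to 70.9) from 45% (25.9 to 65.3). Whether the interval's one-sided error exceeds 5% depends on how one-sided the loss is: at 10% overall loss and a true rate of 50%, it ranges from 3.4% to 8.7% across the three patterns examined. The missing rate and these patterns are assumptions.

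No null rate or success threshold is stated, so no decision rule is invalidated. The harm is to the estimate and interval carried into the next phase. This should be fixed, but it is not a fatal flaw.

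**What to change.** **In 10.3.1 and 10.3.6**, state that all FAS children form the denominator, and that a child without an evaluable 6-month volume counts as a non-responder for both the 20% and the 50% reduction endpoints.

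**Discontinuation MRI.** State in advance, by one rule that applies to every stopping reason, whether this scan may serve as the endpoint scan. A rule that used it only for favourable stops would itself bias the rate.

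**Later treatment.** State that a volume measured after another LM treatment was started does not count as a response. Section 5.5 leaves treatment unrestricted once protocol treatment ends, so shrinkage could otherwise be credited to the study drug wrongly.

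**Sensitivity analyses.** Report the observed-case rate, and best-case and worst-case results for the missing children, beside the primary rate.

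**Cost.** Wording only, with no extra patients and no extra scans. The reported rate will be slightly lower whenever scans are missing, and it will be conservative if some of those children had responded.
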